| Methodology | Single centre, parallel arm randomised controlled trial. Following informed consent, participants will be randomised to 3 cycles of treatment or no treatment. Primary outcome is live birth rate.  Each month participants will be asked to record the first day of their menstrual period. On the relevant cycle day according to the test instructions they will start doing daily LH monitoring using a quantified validated test (same brand) until a positive result is seen. 24hrs later they will start 400mg bd progesterone (Cyclogest) pessaries (vaginal or rectal) and continue these for 14 days. After 7 days they will attend for a serum progesterone level blood test. They will then check a urine pregnancy test (validated, same brand) on the 14^th^ day after starting cyclogest (15^th^ day after LH surge). They will discontinue the progesterone if hcg is negative and those who are pregnant will continue progesterone for 38 days. 2 weeks later they will be offered an early pregnancy ultrasound.  We will gain consent to check NHS records to record live births 42 weeks after the positive pregnancy test. We will ask patients to contact us if they have a miscarriage or late pregnancy loss but will not contact them to chase for information as this does not directly impact on our measurable outcomes (clinical pregnancy rates and live birth rates). |
| Research Sites | Homerton University Hospital |
| Objectives/Aims | To assess whether luteal support with progesterone pessaries affects the likelihood of clinical pregnancy and/or live birth in natural cycles for couples with unexplained infertility |
| Number of participants/patients | 200 in total – 100 in the test group and 100 in the control group |
| Main Inclusion Criteria | Female:   - bilateral patent tubes within last 12 months (HSG/HyCoSy/Laparoscopy) - Ovulation as defined by regular cycles or ultrasound appearance of either a corpus luteum or dominant follicle or midluteal progesterone over 30nmol/ml - Regular intercourse and failure to conceive for at least 12 months   Male:   - Semen analysis with: - >15 mil/ml concentration - Motility over 40% - Progressive motility over 32% - ≥ 4% normal forms - No erectile dysfunction or other problem preventing penetrative intercourse |
| Statistical Analysis & Methodology | Using a baseline expected live birth rate of 7% and an expected live birth rate of 24% in the treatment group, with an α0.05 and 80% power, we need to recruit 70 participants to each group. Allowing for some drop-outs, we will aim to recruit 100 per group. |
| Proposed Start Date | November 2019 |
| Proposed End Date | April 2021 |
| Study Duration | 18 months |

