**Methodology:**

Study design:

This study is a prospective, pragmatic, two-armed, randomised controlled trial. The hypothesised benefit of the luteal phase progesterone support is to enhance endometrial receptivity and improve conception rates measured as clinical pregnancies and eventually live births.

The study does not aim to validate different formulations of progesterone or different dosing regimens. The design of the trial supports the use of progesterone as it is licensed to be used in ART cycles, at a dose of 400mg twice per day either vaginal or rectal application.

This trial will recruit eligible participants meeting the criteria for a diagnosis of unexplained infertility. All new patients seen in the fertility units will be screened for eligibility and if eligible, will be invited to participate. Following informed consent from both partners, participants will be randomised in a 1:1 ratio to either the treatment or control groups. Women will remain in the trial for three menstrual cycles and will be followed up to the end of the third cycle. If pregnant, the outcome of the pregnancy will be recorded at 6-7 weeks of pregnancy when a scan will be performed to determine clinical pregnancy and subsequently by following up live births within 6 weeks postpartum.

Study Population:

The trial will recruit and randomise 200 participants.

Study setting:

Single centre trial at the Homerton Hospital NHS trust Fertility Unit

Inclusion Criteria:

Female:

- Bilateral patent tubes within last 12 months (HSG/HyCoSy/Laparoscopy)
- Ovulation as defined by regular cycles or ultrasound appearance of either a corpus luteum or dominant follicle or midluteal progesterone over 30nmol/ml
- Regular intercourse and failure to conceive for at least 12 months

Male:

- Semen analysis with:
- >15 mil/ml concentration
- Motility over 40%
- Progressive motility over 32%
- ≥ 4% normal forms
- No erectile dysfunction or other problem preventing penetrative intercourse

Exclusion criteria:

- Age ≥42 (as likely component in infertility),
- Unilateral tubal patency
- BMI ≥30
- Abnormal uterine cavity as seen on 3D ultrasound

Primary outcome:

Live birth rates

Secondary Outcome:

Biochemical pregnancy rates (positive urine HCG test at least 14 days after starting progesterone)

Clinical pregnancy (intrauterine gestational sac confirmed on ultrasound at 6-8 weeks gestation)

Mid-luteal serum progesterone levels

Clinical efficacy outcomes/clinical safety outcomes:

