Miscarriage and ectopic pregnancy rates

Stillbirth (pregnancy loss after 24 weeks of gestation)

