**Results Analysis**

Sample size

According to a randomised controlled trial comparing expectant management with stimulated cycle IUI treatment over 3 cycles, 7% of the expectant management group reported live births compared to 24% of the treatment group^7^. The study identified that gave progesterone supplementation in natural cycles also showed a 24% clinical pregnancy rate (live birth rate was not reported).

Using a baseline expected live birth rate of 7% and an expected live birth rate of 24% in the treatment group, with an α0.05 and 80% power, we need to recruit 70 participants to each group. Assuming a drop out rate, we will aim to recruit 100 per group, as was recruited in the Farquhar trial.

Method of Analysis

We have adequate statistical analysis experience within the research team to analyse the data.

Analyses will be intention-to-treat, will include all randomised participants and will analyse according to the treatment group to which they were randomised. For each analysis we will present treatment effect (risk ratio)) along with a 95% confidence interval and a two-side p-value. A P value of <0.5 will be considered statistically significant.

Baseline demographic data will be assumed to be equivalent between the two groups due to the randomisation process.

For each of the outcomes measured (livebirth rate, biochemical pregnancy rates, clinical pregnancy rate, mid-luteal serum progesterone levels and pregnancy loss rates) we will perform a logistic regression, initially doing a univariable regression for each of the potential confounders AMH level, 3 vs no ovulatory cycles according to LH kits, antral follicle count, parity) and combining these together with a variable representing group using lasso or stepwise regression we will perform a multivariable logistic regression analysis.

We will validate the model, looking at calibration and discrimination by providing the c-statistic equivalent to the area under the ROC curve.

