**Safety Reporting:**

Adverse events

An AE is any untoward medical occurrence in a trial participant, including occurrences which are not necessarily caused by or related to the trial intervention. An AE can therefore be any unfavourable and unintended sign (including an abnormal laboratory finding), symptom or disease temporarily associated with trial activities.

Due to the high incidence of adverse events routinely expected in this patient population and the low risk of the intervention, only those adverse events identified as serious will be recorded for the trial.

There are no expected adverse events for this intervention.

Serious Adverse events

A serious adverse event (SAE) is defined as an untoward occurrence that: (a) results in death; (b) is life-threatening; (c) requires hospitalisation or prolongation of existing hospitalisation; (d) results in persistent or significant disability or incapacity; (e) consists of a congenital anomaly or birth defect; or (f) is otherwise considered medically significant by the investigator.

The following events are foreseeable in pregnant women undergoing IVF/ICSI and hence will not require reporting as SAEs.

Events relating to the participant:

1. Ovarian hyperstimulation syndrome

2. Pelvic infection/pelvic inflammatory disease

3. Failure of frozen embryos to survive thawing

4. Multiple pregnancy

5. Miscarriage

6. Ectopic pregnancy

7. Hypertensive disorders of pregnancy

8. Gestational diabetes

9. Antepartum haemorrhage

10. Postpartum haemorrhage

Events relating to the baby:

1. Low/very low birth weight

2. Small/large for gestational age

3. Preterm/very preterm delivery

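### Pregnancy losses are listed and analysed as outcomes, but the synopsis rules out following them up and no other stated route captures them systematically

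*Protocol*

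**What the plan says.** Four places in the protocol bear on this.

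- **Methodology.** Under the heading "Clinical efficacy outcomes/clinical safety outcomes" the protocol lists "Miscarriage and ectopic pregnancy rates", followed by stillbirth, defined as loss after 24 weeks.
- **Results Analysis, Method of Analysis.** The outcomes to be modelled include "mid-luteal serum progesterone levels and pregnancy loss rates".
- **Synopsis, Methodology row.** "We will ask patients to contact us if they have a miscarriage or late pregnancy loss", but the team "will not contact them to chase for information as this does not directly impact on our measurable outcomes". The outcomes counted as measurable are then named as clinical pregnancy and live birth. The same row plans a check of NHS records 42 weeks after the positive test, for the stated purpose of recording live births.
- **Safety Reporting.** Only serious adverse events are recorded, and some of those are then exempted: "The following events are foreseeable in pregnant women undergoing IVF/ICSI and hence will not require reporting as SAEs". Miscarriage and ectopic pregnancy are items 5 and 6 among the participant events. Stillbirth is not on the list.

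**The concern.** An outcome that is modelled by arm under intention-to-treat cannot also fall outside the measurable outcomes and be left without follow-up. The safety route does not close the gap for miscarriage or ectopic pregnancy, because both are exempt. The reason given for the exemption belongs to another population: the list includes ovarian hyperstimulation and frozen embryos failing to survive thawing, while this trial studies natural cycles.

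At stake are the loss rates themselves and the comparison between arms. There is no placebo and the doctors know the allocation. Treated women who conceive continue study medication after the positive test, and controls have no equivalent tie to the team. Reporting could therefore differ by arm, although nothing in the documents shows that it will or in which direction.

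**Working it through.** **Step 1: the routes by which a loss could reach the database.** The protocol gives no figure for loss rates or their capture, so this part is a comparison of text.

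| Route | Where stated | What it can show | Limit |
|---|---|---|---|
| Self-report | Synopsis | Miscarriage, late loss | Requested but not chased; ectopic pregnancy is not named in the request |
| Early scan | Synopsis; Methodology, Study design | Early loss or ectopic pregnancy present by 6-7 weeks | Only offered, according to the synopsis; cannot show later losses |
| NHS-records check | Synopsis | Live birth | Stated for live births; no recorded birth does not say what happened |
| Clinical outcomes from notes | Study Procedures, Data Collection; Case Report Forms | Losses entered in the fertility notes or database | A loss managed elsewhere need not appear there |
| SAE report | Safety Reporting | Stillbirth | Miscarriage and ectopic pregnancy exempt; the team must first learn of the event |

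Study Procedures also ends contact after two unanswered requests. No route assures that a loss after the scan is recorded and classified.

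**Step 2: how many losses are in play (illustration).** From the protocol's sample size: 24 and 7 live births per 100 randomised. Assumption not in the documents: a proportion L of clinical pregnancies is lost, with L between 15% and 25% and equal in both arms. Expected losses per 100 randomised = live births × L / (1 − L).

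- L = 15%: treatment 24 × 0.15/0.85 = 4.2; control 7 × 0.15/0.85 = 1.2
- L = 20%: treatment 24 × 0.20/0.80 = 6.0; control 7 × 0.20/0.80 = 1.75
- L = 25%: treatment 24 × 0.25/0.75 = 8.0; control 7 × 0.25/0.75 = 2.3

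With counts this small, one or two missed events would change the comparison.

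**Step 3: what incomplete capture does (illustration).** Observed ratio = true ratio × (capture in treatment arm / capture in control arm). The capture rates are assumptions, and the true ratio of loss risk among pregnancies is set to 1.

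- Equal capture, 70% or 50% in both arms: ratio 1.0, but at L = 20% the observed risk is 0.20 × 0.7 = 14% or 0.20 × 0.5 = 10%
- 90% v 70%: 0.9/0.7 = 1.29
- 90% v 60%: 0.9/0.6 = 1.5
- 90% v 50%: 0.9/0.5 = 1.8
- Pattern reversed, 70% v 90% or 50% v 90%: 0.78 or 0.56

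Under-capture lowers the rates in every case. Its effect on the ratio depends entirely on the assumed difference between arms.

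**The case against.** The strongest reply is that the protocol has more routes than self-report, and that exempting foreseeable events from SAE reporting while keeping them as outcomes is ordinary practice. Both statements are correct, and they rule out several stronger readings that a reader might infer.

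- *Losses are captured only by self-report.* Not supported. The scan, access to notes for clinical outcomes, and eCRF entry from fertility notes are all stated.
- *Self-report is unprompted.* Not supported. Women are asked to report; what is missing is follow-up.
- *All three harms are outside SAE reporting.* Not supported. Stillbirth is not exempt.
- *The DMC would not see these events.* Not established. Exemption from SAE reporting is not exclusion from outcome data, and the DMC section does not confine the committee to SAE reports.
- *The harm ratio would be biased by a known amount, such as 1.5.* Not supported. That figure follows from assumed reporting rates.

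It can also be said that losses are recoverable by subtraction: biochemical minus clinical pregnancies for losses before the scan, and positive tests minus live births for the total. This stands in part. It gives an approximate total, subject to missed scans and incomplete records. It also depends on home tests that treated women all take but controls take only if their period has not started. It cannot separate miscarriage, ectopic pregnancy and stillbirth, which the protocol lists by name.

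Finally, losses are not among the stated objectives, nor under the primary or secondary outcome headings. That limits the weight of the point but does not remove the contradiction.

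**Conclusion.** The contradiction holds on the protocol's own text. Losses are listed and modelled as outcomes, while the synopsis sets them outside the measurable outcomes and rules out chasing them. The SAE exemption for miscarriage and ectopic pregnancy rests on a rationale that does not fit this trial. If the protocol is followed as written, loss rates are likely to be under-counted, most of all by type and after the scan.

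Unequal under-counting by arm is possible in an open-label design but is not shown. Its size cannot be derived from the documents, and the 1.3-1.8 range and its reverse only show how sensitive the ratio is to the assumed capture rates. Because few losses are expected, the comparison would be imprecise even with full capture. The live birth analysis is not affected. The change should be made, but the trial's main conclusion does not depend on it.

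**What to change.** Reconcile the synopsis, the outcome list in Methodology, Method of Analysis and Safety Reporting:

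1. Remove from the synopsis the statement that losses fall outside the measurable outcomes and will not be chased.
2. For every positive test in both arms, record the pregnancy outcome (miscarriage, ectopic pregnancy, stillbirth or live birth) and its date on the eCRF at the NHS-records check already planned. Match the consent wording to that wider purpose.
3. State that these outcomes are tabulated by arm for the DMC, whether or not they are reported as SAEs.
4. Rewrite the IVF/ICSI exemption text for this trial's natural-cycle population.

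The cost is protocol wording and a few eCRF fields. The records are to be checked for live births in any case, so the extra extraction is small. If present consent covers live births only, the consent form or information sheet may also need a wording change and approval of that change.

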**Introduction:**

Background:

Unexplained infertility affects up to 40% of couples referred to fertility services)^1^. Many theories exist regarding the aetiology of subfertility in these couples; however it is well accepted that the underlying cause is likely to be multi-factorial. The challenges faced with unexplained infertility highlight the need to better understand the aetiology and thus improve treatment outcomes and prognosis.

To be diagnosed with true unexplained infertility, a couple must have proven ovulatory menstrual cycles, patent fallopian tubes and an adequate semen analysis (count, motility and normal forms).

With these parameters tested, and assuming regular sexual intercourse, the current school of thought is that the problem arises at the point of implantation rather than fertilisation. There are however no adequate methods of testing successful fertilisation and thus proving this hypothesis.

Progesterone is a steroid hormone produced initially by the corpus luteum after ovulation and then by a developing early pregnancy. It maintains the oestrogenised, thickened endometrium during the luteal phase of the menstrual cycle and stimulates molecular changes and expression of various receptors and molecules that enhance receptivity of the endometrium to implantation of a developing embryo. Progesterone levels are known to peak seven days after ovulation and then in non-conceptual cycles, slowly decline until the onset of menses. In the UK, it is widely accepted that a progesterone level of 30nmol/L in the mid-luteal phase or on day 7 post-ovulation (usually referred to as day 21 assuming a regular 28-day cycle) indicates successful ovulation. In unstimulated cycles, the level of progesterone on day 21 can vary widely as its release is pulsatile and therefore levels can change over a period of a few hours making a single reading difficult to interpret ^2^.

The relationship between progesterone and endometrial receptivity is multi-faceted. The endometrium is designed to undergo many changes through the menstrual cycle. Estrogen receptor alpha (ERα) is downregulated after ovulation by rising serum levels of progesterone. This allows expression of glycodelin-A (GdA) molecules which are involved in implantation processes. The down-regulation of ERα also allows expression of β3 integrin, a cell-to-cell adhesion molecule also important in implantation and endometrial receptivity.

It has been indicated that in the endometrium of women with unexplained infertility that there is a loss of this progesterone-mediated down-regulation process of the estrogen receptors. This then leads to a reduction in GdA ^3^and β3 integrin^4^ expression, both of which are important for optimising endometrial receptivity and the implantation process.

Rationale:

There is a clear need to investigate the role and effect of progesterone in women with unexplained infertility. We hypothesise that a proportion of women suffering with unexplained infertility have either reduced progesterone production or increased progesterone resistance/ decreased progesterone sensitivity. This in turn affects endometrial receptivity which may reduce the likelihood of implantation.

This randomised controlled trial will be conducted in women with unexplained infertility comparing luteal phase progesterone support in natural cycles with no treatment. Primary outcome measures will be live birth rates. Secondary outcome measures will be clinical pregnancy rates and mid-luteal progesterone levels. To our knowledge, no study has been conducted to date investigating the effect of progesterone support in natural cycles.

Existing Research:

No study has investigated progesterone in natural cycles before. However, one study looking into the effect of ovarian stimulation with or without progesterone support had a control arm which received progesterone in natural cycles. This study, where the inclusion criteria demanded a history of infertility of at least 1 year, showed a 24% live birth rate after treatment for up to 3 cycles^5^. A study comparing luteal phase progesterone support across cycles of IUI using clomiphene, letrozole or clomiphene or letrozole plus gonadotrophins, showed an overall clinical pregnancy rate of 24.1% with progesterone and 14.1% without^6^.

Why this research is urgently needed:

Unexplained infertility affects 40% of couple seeking fertility treatment^1^. If one of the underlying factors is a lack of progesterone or increased progesterone resistance, then the addition of exogenous luteal phase progesterone may aid implantation and improve clinical pregnancy rates and live birth rates.

This intervention is simple, low-risk and inexpensive. Compared to the current treatment options for unexplained infertility, this is a non-invasive and inexpensive intervention.

**Trial Objectives:**

Primary objectives:

The primary objective of this study is to determine whether progesterone luteal phase support results in higher live birth rate than no intervention in natural cycles for couple with unexplained infertility.

Secondary Objectives:

Secondary objectives will be to measure any differences between mid-luteal progesterone levels, and clinical pregnancy rates between the treatment and control groups.

**Methodology:**

Study design:

This study is a prospective, pragmatic, two-armed, randomised controlled trial. The hypothesised benefit of the luteal phase progesterone support is to enhance endometrial receptivity and improve conception rates measured as clinical pregnancies and eventually live births.

The study does not aim to validate different formulations of progesterone or different dosing regimens. The design of the trial supports the use of progesterone as it is licensed to be used in ART cycles, at a dose of 400mg twice per day either vaginal or rectal application.

This trial will recruit eligible participants meeting the criteria for a diagnosis of unexplained infertility. All new patients seen in the fertility units will be screened for eligibility and if eligible, will be invited to participate. Following informed consent from both partners, participants will be randomised in a 1:1 ratio to either the treatment or control groups. Women will remain in the trial for three menstrual cycles and will be followed up to the end of the third cycle. If pregnant, the outcome of the pregnancy will be recorded at 6-7 weeks of pregnancy when a scan will be performed to determine clinical pregnancy and subsequently by following up live births within 6 weeks postpartum.

Study Population:

The trial will recruit and randomise 200 participants.

Study setting:

Single centre trial at the Homerton Hospital NHS trust Fertility Unit

Inclusion Criteria:

Female:

- Bilateral patent tubes within last 12 months (HSG/HyCoSy/Laparoscopy)
- Ovulation as defined by regular cycles or ultrasound appearance of either a corpus luteum or dominant follicle or midluteal progesterone over 30nmol/ml
- Regular intercourse and failure to conceive for at least 12 months

Male:

- Semen analysis with:
- >15 mil/ml concentration
- Motility over 40%
- Progressive motility over 32%
- ≥ 4% normal forms
- No erectile dysfunction or other problem preventing penetrative intercourse

Exclusion criteria:

- Age ≥42 (as likely component in infertility),
- Unilateral tubal patency
- BMI ≥30
- Abnormal uterine cavity as seen on 3D ultrasound

Primary outcome:

Live birth rates

Secondary Outcome:

Biochemical pregnancy rates (positive urine HCG test at least 14 days after starting progesterone)

Clinical pregnancy (intrauterine gestational sac confirmed on ultrasound at 6-8 weeks gestation)

Mid-luteal serum progesterone levels

Clinical efficacy outcomes/clinical safety outcomes:

Miscarriage and ectopic pregnancy rates

Stillbirth (pregnancy loss after 24 weeks of gestation)

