The qualified person taking consent must explain to the potential participants that they are free to refuse any involvement within the study or alternatively withdraw their consent at any point during the study and for any reason. If there is any further safety information that may result in significant changes in the risk/benefit analysis, the patient information sheet (PIS) and Informed Consent Form (ICF) will be reviewed and updated accordingly. All participants that are actively enrolled in the study will be informed of the updated information and given a revised copy of the PIS and ICF in order to confirm their wish to continue in the study (if feasible), if it may change their willingness to participate. Participants who speak limited English can only be consented and included in the trial if translation has been provided by an independent translator (i.e. not a family member) or through the Language Line translation service for UK sites. International sites have the option to translate patient-facing documentation into the required language.

Care Pathway:

Couples with unexplained infertility seen at our unit will be offered the option of self-funded IUI treatment or IVF treatment (NHS or self-funded depending on meeting eligibility criteria). Involvement in this trial will be offered to them as an option prior to self-funded treatment or whilst awaiting NHS-funded IVF treatment for which the waiting time is longer than 3 months.

Randomisation:

A computer programme will be used to randomly allocate each trial ID number to a group and patients will be randomly allocated a trial ID number using choice of a paper ticket.

Blinding: It will not be possible to blind the doctors to whether the patients have received treatment or not. The chief investigator will be responsible for organising prescriptions and given the lack of placebo, will know whether the patient has been allocated to the treatment or control group.

Trial Intervention/allocation:

Participants in the treatment arm will receive 400mg Cyclogest pessaries and will be asked to take these twice a day from 24hrs after their LH surge is detected with ovulation kits. 14 days after starting the Cyclogest they will perform a home pregnancy test and inform us of the results. If they are pregnant they will continue Cyclogest for a further 38 days as pregnancy support.

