Participants in the control arm will record the time of their LH surge and perform a home pregnancy test 14 days later if their next menstrual period has not started.

All participants will be asked to attend the hospital for a mid-luteal serum progesterone test 7 days after the LH surge is detected in the first cycle only.

Monitoring Adherence

Follow-up:

Participants will be asked to email a trial-specific, secure NHS.net email address with details of their cycles – dates for LH positive results and menstrual period start dates. They will use their trial number rather than identifiable personal data. They will have consented to being contacted by either telephone or email to remind them and ask for their data. They will be reminded a maximum of twice per cycle and if they do not respond it will be assumed that they have withdrawn from the trial.

Start dates of each cycle and each LH surge will be recorded. Participants will attend the phlebotomy department at the Homerton for their mid-luteal progesterone and will have consented to the trial team accessing their records to obtain the result.

Data Collection:

The following data will be collected:

Results from hormone profile and tubal patency tests and semen analysis will have been checked prior to consent – this information would be accessed by the clinical team regardless as part of their clinical care.

Basic demographic data, fertility/ menstrual/gynaecological history, relevant medical history, allergies and medication history, dates of menstrual cycles and LH surges and clinical outcomes.

This data is routinely recorded in a patient’s notes and consent will be obtained to access this. Dates of menstrual cycle and LH surges will be requested from patients during the trial.

Identifiable data will be stored in a password protected recruitment log at site but data entered into the database will be pseudo-anonymised (identified only by a participant’s trial ID).

Participant withdrawal:

Participants will have the option to withdraw at any point during the trial and can do so by contacting the team either by email or telephone.

If at any point during the trial, a participant does not reply to two consecutive requests for results it will be assumed that they have withdrawn and no further attempts at contact will be made.

End of Study Definition:

This will be the date six weeks after the expected date of delivery of the last patient randomised who has an ongoing pregnancy.

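### Biochemical pregnancy is dated from a treatment that controls never start, and only controls are excused the test once they bleed, so ascertainment differs by arm

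*Protocol*

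**What the plan says.** The Protocol's Methodology section, under Secondary Outcome, lists "Biochemical pregnancy rates (positive urine HCG test at least 14 days after starting progesterone". No other definition is given for the control arm. The trial is described in the Introduction (Rationale) as "comparing luteal phase progesterone support in natural cycles with no treatment", and the blinding paragraph confirms that there is no placebo.

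The testing instructions are in Study Procedures, under Trial Intervention/allocation:

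- **Treated arm.** Pessaries are used "twice a day from 24hrs after their LH surge is detected with ovulation kits", and "14 days after starting the Cyclogest they will perform a home pregnancy test and inform us of the results". The synopsis places this test "on the 14^th^ day after starting cyclogest (15^th^ day after LH surge". Neither place mentions bleeding.
- **Control arm.** Women record the LH surge and "perform a home pregnancy test 14 days later if their next menstrual period has not started".

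Results Analysis (Method of Analysis) names biochemical pregnancy among the outcomes to be compared, by intention to treat, in all randomised participants.

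On serum progesterone, the synopsis says "After 7 days they will attend for a serum progesterone level blood test", following the instruction to start pessaries and within an account of what happens each month. Study Procedures says that all participants have a "mid-luteal serum progesterone test 7 days after the LH surge is detected in the first cycle only".

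**The concern.** An outcome compared between randomised arms should be defined and looked for in the same way in both. Here the definition needs a date that exists in one arm only, and the test itself is conditional in one arm only.

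The condition is the part that matters. Consider two women with the same event: implantation, a brief rise in hCG, then bleeding before the test day. The treated woman is told to test and may be positive. The control is not asked to test and will in effect be counted as not pregnant. The synopsis also says that pregnancy losses are self-reported and not chased, so there is no dependable second route by which the control's event would come to light. Biochemical pregnancy could then favour progesterone even if progesterone did nothing.

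**Working it through.** **1. Test day on a common clock.** Inputs: progesterone starts 24 hours after the surge (Study Procedures), and the test is 14 days after starting (Study Procedures and synopsis).

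- Treated test day = LH + 1 + 14 = LH+15. This reproduces the synopsis, which states the 15th day after the surge.
- Control test day = LH+14.
- Difference = 15 − 14 = 1 day.

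**2. Can the definition be rescued for controls?** Give a control a notional start at LH+1. Her test then falls on day 14 − 1 = 13 from that start, short of the 14 days required. Read literally, her scheduled test does not meet the definition.

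**3. The two arms side by side.**

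| | Treated | Control |
|---|---|---|
| Progesterone start date for the definition | LH+1 | none |
| Scheduled test | LH+15 | LH+14 |
| Bleeding condition on the test | none stated | tests only if menses have not started |

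**4. Size, by assumption only.** The protocol gives no biochemical pregnancy rate and no share of early pregnancies that bleed before the test. Let s be the share of control positives missed through the bleeding condition, with equal true rates in both arms. Then the observed risk ratio = 1/(1 − s).

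| s (assumed) | Observed ratio when the truth is 1 |
|---|---|
| 5% | 1.05 |
| 10% | 1.11 |
| 20% | 1.25 |
| 25% | 1.33 |
| 30% | 1.43 |

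**5. Per woman over three cycles.** A control missed in one cycle can test positive in a later one. Assume a true rate of 10% per cycle and count a woman as positive if she is ever positive.

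- Treated: 1 − 0.90³ = 0.271.
- Control, s = 10%: detected rate 0.09 per cycle, 1 − 0.91³ = 0.246, ratio 0.271/0.246 = 1.10.
- Control, s = 25%: detected rate 0.075 per cycle, 1 − 0.925³ = 0.209, ratio 0.271/0.209 = 1.30.

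**6. Effect on a significance test.** Take 100 women per arm (the planned number), an assumed true rate of 25% per woman in both arms, and a two-sided 5% test by the normal approximation. If 5%, 10%, 20% or 30% of positive control women are missed, the chance of a significant result favouring progesterone is about 4%, 6%, 13% or 25%, against a nominal 2.5%. Over assumed true rates of 15% to 30%, the range is 3.5% to 31%.

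**7. Serum progesterone.** On its natural reading the synopsis puts the sample at LH + 1 + 7 = LH+8, every month. Study Procedures puts it at LH+7, in the first cycle only, for everyone. The day and the frequency differ between the two places.

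**The case against.** Several points on the other side stand.

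- **Unconditional testing in the treated arm is inferred.** The protocol does not say that treated women test even if they bleed; it attaches no condition. That is still the natural reading, because the synopsis makes stopping progesterone depend on the test result, and because the control instruction shows that the condition was written where it was wanted.
- **The one-day gap has no clear direction.** A reader might infer that testing a day earlier also under-counts controls. An earlier test may be less sensitive, but it may also catch a pregnancy lost between LH+14 and LH+15. Only the bleeding condition has a direction.
- **The drug's effect on bleeding adds nothing here.** A reader might use the Introduction's account of progesterone and menses to argue that pessaries delay bleeding and so enlarge the bias. If treated women test regardless of bleeding, such a delay does not alter their ascertainment. The passage also describes natural progesterone, not pessaries.
- **The illustrative ratio may be too large.** It supposes that a missed control would still have been hCG-positive on the test day. A failing pregnancy may already be negative, as it could be in a treated woman.
- **Distortion of loss rates is not established.** The protocol states no denominator for miscarriage and does not say whether biochemical losses count.
- **Serum progesterone does not run on an arm-specific clock.** Study Procedures already sets one LH-based day and one cycle for all participants. What remains is a conflict between synopsis and body.
- **The outcome is a minor one.** The Rationale and Trial Objectives do not list biochemical pregnancy, although Methodology and Results Analysis do.

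None of this removes the missing control-arm definition or the one-sided bleeding condition.

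**Conclusion.** The point holds in this limited form. As written, the outcome has no meaning for controls, and whether an early pregnancy that bleeds is looked for depends on allocation. The expected direction is towards progesterone. The direction rests on reading the treated arm's instruction as unconditional, and on some early pregnancies bleeding before the test day while hCG is still detectable. The size is not known: 1.11 to 1.33 per cycle, or about 1.10 to 1.30 per woman under the 10% per-cycle assumption, illustrates assumed shares of 10% to 25% and is not an estimate.

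The protocol does not support extending this to the main results. Live birth is little affected, and clinical pregnancy needs a sac on ultrasound at 6 to 8 weeks, which does not depend materially on testing women who have already bled. The change should be made before data are collected, because no statistical analysis plan can restore tests that were not done.

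**What to change.** 1. Define biochemical pregnancy in both arms as a positive urine hCG on or after one common day counted from the LH surge. LH+15, already used in the treated arm, serves for this.
2. Have every woman test on that day in every cycle, whether or not she has bled, and say so explicitly for both arms.
3. Separately, reconcile the synopsis with Study Procedures on the day and the number of cycles for the serum progesterone sample.

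The cost is a change of wording in the protocol and participant information, a few more of the pregnancy tests that the manufacturer is already providing (Finance and Funding gives no quantities), and a small extra burden on controls, who would test in cycles where they have bled. The treated arm's test day and the sample size do not change.
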